## Study Design

A Cluster Randomized Control Trial Study will be conducted. The clusters represent enumeration areas in each kebele.

## Study Subjects

The study participants of this study will be women who are diagnosed to have symptoms of POP and confirmed POP stage I-III through a pelvic examination on paper II of this dissertation proposal.

## Eligibility Criteria

**Inclusion**: Women who will be diagnosed to have symptoms of POP as diagnosed by POP-SS and confirmed POP stage I-III on pelvic examination.

**Exclusion** **Criteria**: Women who were diagnosed to have symptomatic Pelvic Organ Prolapse stage I-III but planned to leave the study area within six months (study period), severely ill women, women with psychiatry disorders, women with delivered myoma, or women who want to have prolapse surgery within six months will be excluded.

## Sample Size Determination

Sample size calculations were performed using Open-Epi version 3.1, based on the following assumptions: a 99% confidence level, 80% power, an exposed-to-unexposed ratio of 1, a POP-SS mean difference of 3.16 with a standard deviation of 4.78 in the intervention group, and a mean difference of 0.12 with a standard deviation of 3.86 in the control group over six months (14). Considering a 16% (15) refusal and loss to follow-up, the effective sample size (individual-based randomization) is 113.4. The decision to adjust the confidence level to 99% was based on the adjusted level of significance to 0.0125 than the usual p-value of 0.05 to account for multiple comparisons across various outcomes (16) (POP-SS and three distinct domains of P-QoL).

The minimum number of clusters needed is calculated by multiplying the effective sample size by the Intra-Cluster Correlation Coefficient (ICC) factors for both groups (17). The estimated fairly typical value of the Intra-Cluster Correlation (ICC) factor is 0.03 (17-19). Accordingly, the minimum required cluster number is 1.67 for each group (intervention and control group). However, to ensure the adequacy of the cluster and to have good power (20, 21), eight clusters (kebeles) will be included in this study. To account for the cluster effect, the effective sample size is multiplied by a Variance Inflation Factor (VIF) of 1.35. The Variance Inflation Factor (VIF) is calculated with the assumption of an equal cluster size. Using Intra-Cluster Correlation value of 0.03, (VIF = 1+ ((n-1) ICC)), where ‘n’ is the average cluster size (17-19). Accordingly, the adjusted sample size is 155 with 19.4 participants per cluster.

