## Data Management and Analysis

Data entry, cleaning, missing data management and descriptive data presentation is similar with Paper-II. In addition, in this paper, to assess the effect of pelvic floor muscle training on prolapse symptoms, an Intention-to-treat (ITT) analysis will be used at the end of six months of training. This analysis will include all women included in the trial study at the beginning and who attended at least one follow-up. A paired t-test will be used to evaluate the mean change from baseline for both groups (intervention and control) groups. Then independent t-test will be used to compare the mean change for the interventional groups against the mean change of the control group as an effect size. The level of significance will be set at a P-value < 0.0125 by using the Bonferroni correction formula for multiple outcomes (16, 29, 30). In this study, there are four outcomes of this single intervention, which included a mean change in prolapse symptoms and three components of prolapse quality of life (Paper IV). Therefore, the level of significance is obtained by dividing the usual P-value (0.05) by a number of statistics to be performed.

A summary of statistics will be computed both at the cluster-level and individual levels for both arms. The presence of cluster effects will be assessed and a multilevel analysis will be considered if a significant ICC value of > 0.5 is detected (31). As an alternative, since the outcome of this study is continuous data, both the cluster-level and individual-level analysis will produce the same result if the cluster size is equal. But if the cluster size is variable, an individual-level analysis weighted by cluster size will be done (20, 21).

This study will use stratified cluster randomization based on geographical locations. This may not balance all possible confounders, especially individual-level factors that may vary across strata. Therefore, the statistical technique of confounder control will be used to control possible confounders at the analysis stage. A Linear Mixed-Effect Model will be used to control confounders in multivariable linear regression. This analysis can increase the statistical power and preferable than the general equation estimation model (GEE) (32). Multicollinarity of the independent variables will be checked before fitting the variable into multivariable linear regression in similar fashion with Paper-II.

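### The stated 80% power for 155 women is not delivered by 8 randomised kebeles (about 45–55% on the plan's own inputs), and the VIF of 1.35 does not fit the stated cluster size

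*Protocol*

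**What the plan says.** All the sizing is in Paper-III, Sample Size Determination; Paper-IV adopts the same number.

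- Error rates: "a 99% confidence level, 80% power, an exposed-to-unexposed ratio of 1".
- Effect: "a POP-SS mean difference of 3.16 with a standard deviation of 4.78 in the intervention group", against "a mean difference of 0.12 with a standard deviation of 3.86 in the control group over six months".
- Individually randomised size: "Considering a 16% (15) refusal and loss to follow-up, the effective sample size (individual-based randomization) is 113.4".
- Clusters: after deriving a minimum of 1.67 per arm, the section decides that "eight clusters (kebeles) will be included in this study". The flow diagram under Randomization shows 4 clusters and 78 women per arm.
- Cluster adjustment: "the effective sample size is multiplied by a Variance Inflation Factor (VIF) of 1.35". The formula given is VIF = 1 + (n − 1) × ICC, with n the average cluster size and ICC 0.03.
- Result: "Accordingly, the adjusted sample size is 155 with 19.4 participants per cluster".

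For testing, Paper-III, Data Management and Analysis uses a different level from the sizing: "The level of significance will be set at a P-value < 0.0125 by using the Bonferroni correction formula for multiple outcomes".

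**The concern.** The paragraph accounts for clustering only through the VIF. A VIF corrects the variance of the difference between arms. It does not correct for the fact that this variance must be estimated from 8 units. With 4 kebeles per arm, the reference distribution is far from normal in the tails, and a small alpha magnifies the gap. The paragraph makes no allowance for this.

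The VIF itself also clashes with the cluster size reported two sentences later.

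At stake is the trial's headline design property. If power for the assumed effect is near one half, a non-significant result says little about the training. The protocol's readers, and those of Paper-IV, are told otherwise.

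**Working it through.** **Inputs.** All come from Paper-III, Sample Size Determination, except the test level 0.0125 (Data Management and Analysis). Sidedness is not stated; I assume two-sided. Difference between arms: 3.16 − 0.12 = 3.04. Sum of variances: 4.78² + 3.86² = 37.75.

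**1. Reproducing 113.4.** n per arm = 37.75 × (2.576 + 0.842)² / 3.04² = 47.7. Two arms divided by 0.84: 2 × 47.7 / 0.84 = 113.6. The stated figure reproduces, with normal quantiles at alpha 0.01.

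**2. The VIF.** A VIF of 1.35 needs n = (1.35 − 1)/0.03 + 1 = 12.7. At 19.4 the plan's formula gives 1 + 18.4 × 0.03 = 1.55. With 8 kebeles, n depends on the total N, so both must be solved together:
- VIF on enrolled cluster size: N = 113.4 × 0.97 / (1 − 113.4 × 0.03/8) = 191 (23.9 per kebele).
- VIF on analysed cluster size: 95.4 × 0.97 / (1 − 95.4 × 0.03/8) = 144 analysed, and 144/0.84 = 172 enrolled.

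**3. Standard error at 155 enrolled.** Analysed: 155 × 0.84 = 130.2, or 16.3 per kebele. VIF = 1 + 15.3 × 0.03 = 1.46. SE = √(37.75 × 1.458 / 65.1) = 0.920. Noncentrality = 3.04 / 0.920 = 3.31.

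**4. Power.** Large-sample power uses the normal cut-offs 2.58 (alpha 0.01) and 2.50 (alpha 0.0125). Comparing 4 with 4 kebeles leaves 8 − 2 = 6 df, with cut-offs 3.71 and 3.52; power is then from the noncentral t.

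| Analysed | VIF | Alpha | Normal | t, 6 df |
|---|---|---|---|---|
| 130 (16% lost) | 1.46 | 0.01 | 77% | 44% |
| 130 (16% lost) | 1.46 | 0.0125 | 79% | 49% |
| 155 (none lost) | 1.55 | 0.01 | 82% | 49% |
| 155 (none lost) | 1.55 | 0.0125 | 84% | 54% |

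**5. Detectable difference.** At 0.0125 with 6 df, 80% power needs a noncentrality of 4.56: 4.56 × 0.920 = 4.2 points.

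**6. Sensitivity to the ICC.** The plan gives only 0.03. Over an assumed range of 0.01 to 0.10, with 130 analysed, 6 df and alpha 0.0125, power falls from 60% to 27%.

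**7. Sensitivity to the number of women.** With 136 enrolled and 16% lost (114 analysed, VIF 1.40), power on 6 df is 40% at 0.01 and 45% at 0.0125.

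**The case against.** **The VIF slip is small.** This stands. Sizing at 0.01 but testing at 0.0125 nearly offsets it: at 0.0125, with the VIF on analysed cluster size, the self-consistent size is about 134 analysed or 160 enrolled, against 155. A reader might infer that the VIF error halves the power. It does not; row 2 of the table still shows 79% before degrees of freedom are considered.

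**191 is not simply the number required.** This also stands. The 113.4 already includes the 16% allowance, so putting the enrolled cluster size into the VIF counts women who give no outcome. On the analysed basis the figure is 172. Neither size restores 80% once 6 df are used: in 8 kebeles that would take about 453 analysed at 0.0125.

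**The 49% is conditional.** It takes a simple two-sample comparison on 6 df. It credits no gain from stratification or covariates, and charges all of the 16%, which the plan describes as refusal and loss together, after enrolment. With nobody lost it is 54%. Charging 3 further df to the four strata gives about 25% at 0.0125, before any gain in precision. These points argue for a stated range, not for 80%.

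**The planned analysis may look better powered.** Data Management and Analysis plans an independent t-test on women, and considers multilevel analysis only if the ICC exceeds 0.5; a mixed model is named for confounder control. A reader might infer that the planned t-test has only half power. In fact its nominal power would be near or above 80%, but without control of type I error: it understates the SE by √1.46 = 1.21, so its cut-off of 2.50 acts as about 2.07, a real level near 3.9% rather than 1.25%. That does not support the 80% claim.

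**The unit is not settled.** Paper-III's Study Design and Description of Intervention call the cluster an enumeration area, to which 6 df would not apply. But the sample size section, Randomization and the flow diagram all randomise kebeles, and the sizing is built on 8 of them.

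**Conclusion.** The 80% claim is wrong as written. With kebeles randomised, the plan's own inputs and 155 enrolled, a comparison that respects the randomisation has about 45–55% power for 3.04 points, across alpha 0.01 or 0.0125 and 16% or no loss. At 0.0125 with 16% loss it detects about 4.2 points with 80% power. Power stays below 80% over the whole assumed ICC range of 0.01–0.10. Nearly all of the shortfall comes from having 4 kebeles per arm; the VIF mismatch is a real but secondary error. The exact figure rests on a two-sided test, 6 df, ICC 0.03, no precision gained from strata or covariates, and the number of women finally confirmed.

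**What to change.** First reconcile two things on which the restated power depends:
- The randomised unit: kebele in Sample Size Determination and Randomization, enumeration area in Study Design and Description of Intervention.
- The number of women: 155 in the sample size section and 78 per arm (156) in the flow diagram; 136 in the Summary, Description of Intervention and Budget; 130 in Paper-IV, Data Collection Tools and Procedures.

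Then, for 8 kebeles and 155 women:
- Keep the number of women and give the VIF at the actual cluster size: 1.55 enrolled, 1.46 analysed.
- Compute power from the t distribution with 6 df.
- Replace the 80% claim with about 45–55% power for 3.04 points, stating the ICC, loss and alpha, and about 4.2 points detectable with 80% power at 0.0125.

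If 136 is confirmed instead, the power to state is about 40–45%.

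This rewrites one paragraph and aligns a few numbers. It needs no extra women. The downside is a less favourable stated power.

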## Randomization

The study site, Hawassa University Demographic and Health Survey sites, comprises eight kebeles from Dale district and four kebeles from Wonsho district. In this study, these kebeles will be stratified into four strata based on their geographical location (Dale-Urban, Dale-Rural, Wonsho-Urban, and Wonsho-Rural). Stratifying on location reduces stratum variability and helps to ensure that they are balanced across study arms (20, 21). To improve similarity across treatment and control groups, the same number of clusters from each strata will be assigned to each arm. Accordingly, four clusters/kebeles from Rural-Dale will be assigned to each arm by lottery method. Similarly, two kebeles/clusters from rural-Wonsho will be assigned to each arm. The two urban kebeles will be assigned to each arm by lottery method. To reduce the risk of information contamination, the interventional and control clusters will be separated by a buffer zone (20), at least one kebele (Figure 4).

**Dale-Wonsho DHSS = 12 kebeles**

Wonsho-Rural (3) kebele

Dale-Rural (7) () kebele

Dale-Urban 1

Wonsho-Urban 1

Select 2 kebele

Select 1kebele women

Select 1kebele women

Select 4 kebeles women

1kebele

1 kebele

2kebele

2kebele

Intervention group (cluster=4, n= 78)

Control group (cluster=4, n= 78)

Received counselling & Training (n= -)

Received Counselling (n= -)

Analyzed at six months (n= -)

Analyzed at six months (n= -)

Loss to follow-up (n= -)

Loss to follow-up (n= -)

Dale-district 8 kebeles

Wonsho district 4 kebeles

1kebele

1kebele

**Stratified**

**Stratified**

**Selection** **Probability**

**SR**S

**SRS**

Figure 1: Flow diagram for the cluster randomized control trial study on Effect of Pelvic Muscle Training on Prolapse symptom in Sidama Region, Ethiopia, 2022.

## Description of Intervention

From each selected health facility, two female Nurses or Midwives will be trained on Pelvic Floor Muscle Training and how to counsel patients. The training will be given for nurses and midwives by urogynaecologist. The training will have a theory, simulation, and video aids.

Among women diagnosed to have symptomatic stage I-III pelvic organ prolapse, 136 will be assigned to the interventional and control groups based on their pre-assigned enumeration area (cluster). Those assigned to intervention will receive pelvic floor muscle training and prolapse lifestyle advice focusing on constipation, chronic coughing, heavy lifting, and other medical conditions. The control group will receive only lifestyle modification but not trained on pelvic floor muscle exercise. The detailed counselling will be provided using a translated Sidaamu Afoo version of a leaflet (Annex-IV) (22).

In the interventional group, at the initial visit, women will be informed about their stage of POP, type of prolapse (anterior, posterior, or central), the advantage of pelvic floor muscle exercise, and how it works. The detail of the exercise and follow-up schedule will be explained in detail in a private room for 30-40minutes. They will be trained to sit or lie comfortably, train pelvic muscles with 10 times 10-second maximum holds, and 10 fast contractions. This will be repeated at least three times per day (morning, afternoon, and night) (14, 22). They will be invited to attend five visits (at weeks 0, 2, 6, 10, and 15) at a nearby health facility. Five visits are preferred because 15-weeks intensive training is recommended to get adequate muscle strength) (23).

At the initial visit, they will be given a diary where they record (tally) the duration and frequency of exercise they practiced. In case they cannot make a tally, a different color and size of buttons will be provided (larger black buttons represent a number of days per week they perform the training, medium red buttons represent the frequency of training performed per day and the white small buttons represent the number of contractions performed). They will put buttons in a given box each day they perform the training and this will be checked on each visit. To ensure participants' follow-up, the respective pelvic muscle trainer will remind them two days before the appointment day through women’s phone or their respective Health Extension workers. In addition, transportation costs and time compensation will be covered by the research team. In a case where the participant cannot attend the visit, the PFM trainer will visit her at home. The change in prolapse symptoms will be analyzed at six months.

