**Methods:** This study will be conducted in two phases. Initially, the pelvic organ prolapse Symptom Score questionnaire will be translated into Sidaamu Afoo and evaluated for its psychometric properties on a sample of 70 women with pelvic organ prolapse recruited from the gynecology outpatients of Adare General Hospital and Yirgalem Hamline Fistula Center from May 1-25, 2022. Then a complex sample survey will be conducted to establish the prevalence of prolapse based on a sample size of 816 women. It will be conducted in eight kebeles of the Dale and the Wonsho districts from June 1–July 30, 2022. A multistage stratified sampling technique will be used to recruit study participants. The data will be collected through face-to-face interviews with the selected women at the household level. Then all women will be invited to have a pelvic examination at a nearby health facility where the prevalence of the prolapse will be determined by pelvic examination. A complex sample survey analysis will be used to determine the prevalence and determinants of pelvic organ prolapse. In the second phase of the project, a cluster-randomized controlled trial study will be conducted to evaluate the effect of pelvic floor muscle training for the reduction of prolapse symptoms and improving quality of life among 136 (68 participants in each arm). The health-related quality of life will be assessed by using a translated Sidaamu Afoo version of the Prolapse Quality of Life tool, validated in the Amharic version. A Student t-test will be used to evaluate the mean change between the two groups (control and intervention), both for prolapse symptoms and quality of life separately. Linear Mixed-effect Model will be used to control potential confounders in multivariable linear regression for both outcomes.

**Work Plan and Budget**: This study will be conducted from April to November 2022. A total of **762, 295** Ethiopian Birr **($15,245.9)** is needed to conduct this study.

**Key terms:** Ethiopia, Pelvic Organ Prolapse, prolapse, POP, quality of life, pelvic floor muscle exercise, PFMT, pelvic muscle training

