Data collection will be conducted in two phases. The baseline data will be collected from 130 symptomatic POP stage I-III participants at the health facility immediately as soon as they are diagnosed with POP (Paper-II). The data will be collected through face-to-face interviews by the same person who perform pelvic examination from 01 June – 24 July 2022. The end-line data will be collected after six months of intervention. The data will be collected at the household level by data collectors who know the house of these participants. These data collectors will be those who collected the data at the beginning of the study (Paper-II).

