# **BUDGET**

Table 5: Budget Breakdown for the study conducted on Pe/vic Organ Prolapse in Sidama Region, Ethiopia, 2022.

| S. no | Item | Unit | Quantity | Cost/unit (ETB) | Multiplication | Total in ETB and (American Dollar) |
| --- | --- | --- | --- | --- | --- | --- |
|  | Ethical clearance | Proposal | 01 | 300 |  | 300 ($6) |
|  | Tool translation | Person | 02 | 359 | 5days | 3590($71.8) |
|  | Questionnaire duplication | Page | 20 | 2 | 857 | 34,280($685.6) |
|  | Data collection training | Person | 20 | 359 | 05 days | 35,900 ($718) |
|  | Hall rent | Room | 01 | 1000 | 03 days | 3000 ($60) |
|  | Refreshment | Person | 20 | 150 | 03 days | 9,000 ($180) |
|  | Transportation | Person | 20 | 100 | 2 round | 4000 ($80) |
|  | Trainer perdiem | Person | 02 | 1500 | 03 days | 9000 ($180) |
|  | Data collector perdiam | Person | 16 | 359 | 10 days | 57,440 ($1,149) |
|  | Women transportation | Person | 816 | 300 |  | 244,800 ($4,896) |
|  | Pelvic examiner | Person | 2 | 1500 | 30 days | 90,000 ($1,800) |
|  | Tool validation | Person | 2 | 300 | 50patient | 30,000 ($600) |
|  | Mask and Sanitizer | Person | 15 | 100 |  | 1500 ($30) |
|  | Speculum rent | Each | 816 | 20 |  | 16,320($326.4) |
|  | Sub-total 1 |  |  |  |  | **539,130 ($10,782.6)** |
|  | **PHASE**-II | | | | | |
|  | PFMT trainer | Person | 4 | 1000 | 10 days | 40,000 ($800) |
|  | Follow-up transportation | Person | 136 | 200 | 4 round | 108,800 ($2,176) |
|  | End line assessment | Person | 8 | 359 | 5 days | 12,565 ($251.3) |
|  | Supervisor per diam | Person | 02 | 359 | 40 days | 28,720 ($574.4) |
|  | Data entry (clerk) | Person | 02 | 359 | 10 days | 7,180 ($143.6) |
|  | Mobile card | Person | 15 | 200 |  | 3000 ($60) |
|  | Glove | Pack | 18 | 800 |  | 14400 ($288) |
|  | Spatula | Pack | 09 | 500 |  | 4500 ($90) |
|  | Pen and note pad | Each | 100 | 40 |  | 4,000 ($80) |
|  | Sub-total 2 |  |  |  |  | **223,165 ($4,463.3)** |
|  | Ground total |  |  |  |  | **762, 295 ($15,245.9)** |

****** $1 = 50 Ethiopian birr

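### The protocol gives three incompatible trial sizes (155, 136 and 130); if the assignment figure of 136 is followed, the trial falls 12% short of its own calculation

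*Protocol*

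**What the plan says.** Each of these figures stands in the current body of the protocol:

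- **155.** Paper-III, Sample Size Determination: "Accordingly, the adjusted sample size is 155 with 19.4 participants per cluster".
- **78 per arm.** The Paper-III flow diagram, for example "Control group (cluster=4, n= 78" and the same for the intervention arm. This is 155 rounded up to equal arms (2 × 78 = 156), not a further figure in conflict.
- **136.** Paper-III, Description of Intervention: "136 will be assigned to the interventional and control groups". The Summary agrees, "improving quality of life among 136 (68 participants in each arm", and so does the Phase-II part of the budget, "Follow-up transportation | Person | 136 | 200 | 4 round".
- **130.** Paper-IV, Data Collection Tools and Procedures: "The baseline data will be collected from 130 symptomatic POP stage I-III participants".

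Paper-IV is not a separate trial. Its design section refers back to Paper-III for subjects and randomization, and its own sample size section says that the size was based on Paper-III.

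**The concern.** The number of women to enrol is a basic design quantity, and the power claim is tied to it. The calculation and the flow diagram support one figure. The lower figures stand in the text on assigning women to arms, on the Paper-IV baseline and on follow-up transport. A team that works from that text could enrol fewer women than the calculation requires and believe that it had followed the protocol.

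A sponsor, ethics committee or later reader also cannot tell which size was planned. Any comparison of achieved with planned enrolment would then depend on which page is cited.

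**Working it through.** **Inputs** (Paper-III, Sample Size Determination): "a 99% confidence level, 80% power, an exposed-to-unexposed ratio of 1"; mean change 3.16 (SD 4.78) with intervention and 0.12 (SD 3.86) with control; 16% refusal and loss; VIF 1.35; eight clusters. Sidedness is not stated, so two-sided is assumed.

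**Step 1: reproduce the plan's figure.**
- Difference: 3.16 − 0.12 = 3.04. Sum of variances: 4.78² + 3.86² = 37.75.
- Per arm: n = 37.75 × (2.576 + 0.842)² / 3.04² = 47.7, rounded up to 48.
- Total allowing for loss: 2 × 47.7 / 0.84 = 113.6, or 2 × 48 / 0.84 = 114.3. The protocol states 113.4.
- Times the VIF of 1.35: 113.4 gives 153.1, 113.6 gives 153.3 and 114.3 gives 154.3. The protocol states 155, so the figure reproduces to within two women.

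**Step 2: look for an origin of 136 or 130.** With the stated VIF of 1.35:
- adding the loss as n × 1.16 gives about 149 (2 × 47.7 × 1.16 × 1.35);
- a level of 0.0125 gives 146.4;
- a level of 0.05 gives 103.0.

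None gives 136 or 130. An unstated VIF of 1.20 would give 136.3 at level 0.01 and 130.1 at level 0.0125. The protocol does not use 1.20, so this shows only that such figures can be reached with other inputs. Also, 155 × 0.84 = 130.2, which might suggest women remaining after loss, but 130 is given for baseline collection, before any loss to follow-up.

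**Step 3: size of the shortfall.**
- 155 − 136 = 19, and 19/155 = 12.3%.
- 155 − 130 = 25, and 25/155 = 16.1%.

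**Step 4: power on the plan's own basis.** Effective n per arm = (N/2) × 0.84 / 1.35. Power = Φ(3.04 / √(37.75/n) − z), with z = 2.576 at level 0.01. The last column uses the analysis level from Data Management and Analysis: "The level of significance will be set at a P-value < 0.0125 by using the Bonferroni correction formula for multiple outcomes".

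| N | Effective n per arm | Power, level 0.01 | Power, level 0.0125 |
|---|---|---|---|
| 155 | 48.2 | 80.5% | 82.6% |
| 136 | 42.3 | 74.0% | 76.5% |
| 130 | 40.4 | 71.6% | 74.2% |

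At either level 155 meets the 80% target, and 136 and 130 do not.

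**Step 5: transport budget.** 136 × 200 × 4 = 108,800 ETB, as budgeted. 156 × 200 × 4 = 124,800 ETB, which is 16,000 ETB more (320 dollars at the protocol's 50 ETB per dollar).

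**The case against.** The best defence is that this is leftover text. The sample size section and the flow diagram agree with each other, and the sentence with 136 describes the intervention and sets no recruitment cap. On that view 136 and 130 are stale counts, and the planned size is 155.

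Much of this stands, and it limits what may be inferred. Four stronger readings are tempting but not supported:

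- **That the trial would stop at 136.** This depends on which part of the protocol staff follow. The flow diagram tells them 78 per arm.
- **That up to 26 women would lack a baseline P-QoL and hence a change score.** This requires 156 enrolled and a strict limit of 130 interviews; with 136 enrolled the gap would be at most 6. No limit is stated. Paper-II's data collection section and Part X of the English questionnaire give the P-QoL to women with confirmed prolapse generally, and Paper-IV times it at diagnosis. Paper-II's multiple imputation for missing data also carries over to Papers III and IV.
- **That power is really 43% to 49%.** Those values come from a t reference on 6 degrees of freedom for eight kebeles. That is a separate question about few clusters, and it applies at 155 as well.
- **That there are four conflicting sizes.** 156 is only 155 rounded to equal arms.

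The defence does not remove the contradiction. 136 appears in three places, including the statement of how many women are assigned, and no text says which figure governs.

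**Conclusion.** The point holds as an unreconciled contradiction in a figure on which the trial relies: 155 (78 per arm), 136 and 130. It is more than clerical, because the number assigned determines whether the stated power is reached. If 136 is followed, enrolment is 12.3% below the plan's own calculation and power is about 74% (about 72% at 130) against the stated 80%. The loss against 155 is moderate, about 6.5 percentage points.

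These power figures assume a two-sided level of 0.01, 16% loss, a normal approximation and the protocol's VIF of 1.35 at every size. They measure the effect of the discrepancy and do not endorse 155 as sufficient. The protocol's own formula at 19.4 women per cluster gives 1 + 18.4 × 0.03 = 1.55, not 1.35. With a design effect matched to each cluster size (N/8), power at level 0.01 is about 73.5% at 155 and 69.1% at 136. That is a separate point; the direction here is the same either way.

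**What to change.** Use one enrolment figure throughout, taken from Paper-III's Sample Size Determination (currently 155, or 78 per arm):

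1. Replace 136, and 68 per arm, in the Summary, and 136 in Paper-III's Description of Intervention.
2. Replace 130 in Paper-IV's Data Collection Tools and Procedures, and state there that baseline P-QoL is taken from every enrolled woman, in line with Paper-II and Part X of the questionnaire.
3. Update the follow-up transport line in the budget, with the subtotal and grand total. The increase is at most about 16,000 ETB if both arms travel. If the line is meant for the intervention arm only, 78 × 200 × 4 = 62,400 ETB is already covered; the protocol should say which applies.

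If the sponsor prefers 136, it should say so everywhere and restate the power as about 74% on the plan's own basis. If the VIF is revised, settle that first and carry the resulting figure through the same places.

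The cost is a few text edits and, at most, the transport sum above. The recruitment source, the 816-woman survey, does not change.
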